#### Cognitive behavioural therapy for insomnia (CBTI) and partner-assisted CBTI (PA-CBTI)

We employ a CBTI protocol based on those recommended by the leading experts in the field [40, 41]. This protocol covers the four-factor model of insomnia, sleep restriction, stimulus control, sleep hygiene, stress and relaxation, cognitions and sleep, and relapse prevention. PA-CBTI follows the same session outline as CBTI. The “partner-assisted” aspect involves: (a) teaching the partner all of the same concepts and psychoeducation as provided to the client; (b) providing handouts of session material tailored specifically for the partner; (b) actively engaging the partner in all treatment-related decision making and problem-solving; and (d) actively engaging the partner in determining how they can assist the client to implement treatment recommendations at home and assigning those behaviours as the partner’s homework. For example, we engage the partner along with the client in reviewing sleep diaries of the client, identifying patterns, deciding on changes to make, and determining whether/how to titrate time-in-bed for the coming week. The partner also actively assists the client to pick bed/wake times, activities and locations related to stimulus control principles, and strategies for staying awake and/or avoiding naps, etc. In essence, anything a client does in traditional CBTI is done with input from the partner in PA-CBTI. The therapist emphasises empowerment of the partner to provide support and structure for the client at home to maximise adherence to the intervention.

#### Partner-assisted sleep management therapy (PA-SMT)

Sleep management therapy includes all aspects of CBTI, except sleep restriction therapy and stimulus control: the 3P model of insomnia, sleep hygiene, stress and relaxation, cognitions and sleep, and relapse prevention. We use the 3P model in PA-SMT because it does not include conditioned arousal as the fourth factor, as this factor is intimately tied to stimulus control. While the primary goal of this study is to compare PA-CBTI with i-CBTI regarding adherence and attrition, inclusion of a non-active control arm facilitates interpretation of results. Specifically, PA-SMT will help control for the interaction of non-specific therapy factors and the involvement of the partner. We expect this condition to show high adherence without conferring benefits to sleep. This is also a valuable control because sleep hygiene (the core of SMT) is the only treatment many individuals with insomnia are offered given that CBTI is typically is only available in specialty clinics. If results indicate that adding the partner increases adherence (as expected) and this, in turn, increases sleep outcomes, PA-SMT would be a much more cost effective way of treating sleep problems than i-CBTI or PA-CBTI. To be clear, we do not expect that outcome, but it would be remiss not to examine for it. In PA-SMT, a different topic is covered in each session, including education about sleep-wake cycle, sleep hygiene, exercise, diet, alcohol, and caffeine. Sleep restriction and stimulus control principles are strictly avoided. Prior studies have shown that SMT is a credible and well-accepted intervention, though it does not improve sleep [43, 43].

### Fidelity

Manuals are used in all treatment sessions with the psychologist to ensure treatment fidelity, and specific training is provided to all clinicians for all manuals. To ensure fidelity to the delivery of treatment, all sessions are audio recorded. Treatment fidelity is emphasised in several ways: (a) therapists receive intensive training on all interventions; (b) therapists receive weekly group supervision, including the supervisor listening to selections of that week’s audio recordings; and (c) audio recordings of every session from the first two cases of each treatment and 10% of all subsequent sessions are evaluated for treatment fidelity (based on standardised check lists of session content).

### Outcome measures

#### Primary outcome measures

Assessments include: (a) major assessments conducted pre- and post-treatment and at 6-month follow-up for both the client and partner; and (b) weekly and daily assessments for the client as shown in Table 2.

**Table 2 Tab2:**
[figure not shown]
Schedule of enrolment, intervention, and assessments for Project REST. *C* client, *CBTI* cognitive behavioural therapy for insomnia, *fu* follow-up, *I* individual, *P* partner, *PA* partner-assisted, *SMT* sleep management therapy, *tx* treatment

Primary outcome variables include treatment adherence to sleep restriction and stimulus control, as assessed by sleep diaries, clinician-rated adherence forms, and treatment completion rates.

##### Sleep diaries

Sleep diaries are widely used in studies of insomnia [44]. Each morning, participants are asked to record sleep habits such as bedtime, wake time, time in bed, and number and duration of awakenings and naps. Weekly averages are calculated. Sleep diaries include questions to track treatment adherence. Adherence to sleep restriction is calculated as average nightly deviation, in minutes, between the prescribed bed/wake times and reported times, plus any nap time [41, 45]. Note that, consistent with sleep restriction, clients are not considered “non-adherent” if they go to bed later or wake up and get out of bed earlier than scheduled times as they are taught this will simply increase sleep debt and aid treatment. Stimulus control adherence involves two questions: the first asking how many wake minutes after lights-out were spent out of bed (we then calculate that as a proportion of total wake minutes), and the second asking how many minutes outside the sleep window were spent in bed doing any activity other than sleep. Sleep management therapy adherence is measured by documenting the extent to which the treatment recommendation(s) to be practised each week is followed. Additionally, adherence to sleep restriction and stimulus control will still be calculated, despite these not being treatment recommendations. Hence, this group serves as a control for how much these behaviours change without a specific focus on them. While having several measures of adherence poses analytical challenges, the advantage is it allows us to assess exactly where, if anywhere, adherence fails. Adherence measures are obtained in sessions 3–7 (changes to sleep commence at session 2). We considered also using actigraphy to assess adherence (i.e. objective measure of bed time/wake time in sleep restriction). However, we decided against this, since actigraphy cannot measure stimulus control (i.e. cannot determine whether motion is in or out of bed) or assess sleep hygiene.

##### Client adherence form (CAF)

The CAF was created for the US Veterans Affairs CBTI training program using an expert consensus process. Using a scale of 1 to 6 (no adherence to complete adherence) or not applicable (for strategies not yet taught), therapists rate client adherence on six specific CBTI activities [22]. A modified version has been developed for this trial, including for PA-SMT. Clinicians complete this form after each treatment session every week.

#### Secondary outcome measures

##### Sleep measures

The Insomnia Severity Index (ISI) consists of seven items assessing severity of insomnia in the past week [46, 47].

Using the sleep diary, diary-calculated sleep efficiency, time spent awake after sleep onset, sleep onset latency, and early morning awakenings are secondary outcome variables. These variables are calculated both as weekly averages and as night-to-night variability measures.

Actigraphy, an objective measure, is not part of the diagnostic criteria for insomnia. However, these data are commonly reported in insomnia studies and will provide data for secondary analyses. Participants wear the Actiwatch Spectrum Pro (Philips Respironics) either throughout treatment as well as for 1 week prior to the 6-month follow-up (clients) or for 1 week at each assessment time point (partners). Actiwatch data are collected in 30-s epochs in its standard sensitivity wake threshold (score wake at more than 40 activity counts per epoch) and scored using the Cole-Kripke algorithm. Weekly averages are calculated.

##### Relationship measures

The Dyadic Adjustment Scale (DAS; [48]) is a widely used 32-item inventory with sound psychometric properties of relationship adjustment in couples.

The Communication Patterns Questionnaire (CPQ; [49]) is a widely used 23-item self-report measure assessing couple communication before, during, and following discussion of relationship problems.

##### Comorbid psychopathology

The Patient Health Questionnaire-9 (PHQ-9 [50]) is a 9-item questionnaire assessing severity and frequency of depression symptoms.

The Posttraumatic Stress Disorder Checklist-5 (PCL-5 [51]) consists of 17 items assessing trauma symptoms based on DSM-5 criteria.

The Beck Anxiety Inventory (BAI [52]) has 21 items assessing general anxiety symptom severity.

The Quality of Life Enjoyment and Satisfaction Questionnaire Short Form (Q-LES-Q-SF; [53]) is a 16-item self-report questionnaire assessing quality of life on multiple domains.

Each of these measures are given during major assessments.

##### Treatment expectations and satisfaction

Since client and/or therapist expectations could impact outcomes, both will complete expectation measures after the first session using the Treatment Credibility/Expectancy Questionnaire. Data will be examined as a possible mediator of outcomes.

The Client Satisfaction Questionnaire (CSQ; [54]) is an 8-item questionnaire that provides a measure of client satisfaction with services received.

#### Allocation to treatment conditions

Participants are randomised to one of three treatment conditions. Randomisation occurs within clinicians such that each clinician sees an equal number of clients in each treatment condition. Randomisation occurs separately for male and female clients to help ensure equal male:female ratios for each treatment condition.

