#### Statistical tests of hypotheses

##### Aim 1

Hypothesis 1A predicts that individuals under partner-assisted conditions will show greater adherence and lower attrition than those under the individual treatment condition. We will test this with 3 × 5 (group × session) MANOVA. The MANOVA will first test the entire set of adherence variables by constructing a latent variable of adherence and using this as the outcome variable. If significant, we will then examine the univariate results for each specific adherence measure. Significant main effects of group (the hypothesised effect) will be followed by comparing PA-CBTI with each of the other groups. Hypothesis 1B will use the Chi-squared test to test the proportion of participants who complete each treatment, with similar follow-ups.

##### Aim 2

Hypothesis 2A anticipates that greater adherence will relate to better sleep outcomes in PA-CBTI and i-CBTI, but not PA-SMT. Multiple regressions will test the hypothesis, with explanatory variables of group (dummy coded), adherence (in the last week of treatment), and group × adherence interaction. The outcome variable will be diary-derived sleep efficiency in the last week of treatment. The interaction term is the effect of interest. Follow-ups will examine the adherence effect within each group. Hypothesis 2B will be tested with Sobel mediation. We hypothesise that PA-CBTI will show (via sleep diaries) greater mean daily sleep efficiency at post-treatment and 6-month follow-up compared with i-CBTI. This effect will be mediated by adherence at the end of treatment (adherence cannot be measured at follow-up since we will not be prescribing sleep schedules).

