### Limitations

A limitation of the current study is that neither clients nor clinicians are blinded to the treatment condition, a problem inherent to any intervention of psychotherapy. However, clients are blinded to the study hypotheses and staff who score polysomnography, actigraphy, and questionnaires are blind to treatment condition.

In addition, because we want to be reflective of a clinic-based population, and for the sake of feasibility and to reduce participant burden, the ‘baseline’ sleep diary and actigraphy data are collected between weeks 1–2 of treatment. Hence, this may not be considered as a true baseline. However, between weeks 1–2 the active intervention has not yet commenced as the first session consists of education only. Similarly, our ‘post-treatment’ sleep diary and actigraphy data are collected between weeks 6–7 of treatment. However, the final treatment session is a summary session only and no additional treatment strategies are introduced. All other post-treatment data (e.g. questionnaires) are collected after completion of treatment session 7.

We do not conduct a diagnostic assessment in the partners. Thus, it is possible some of them meet the criteria for a sleep disorder. While we considered conducting such screens, conceptually we do not believe the presence of a sleep disorder should have an impact on the partner’s ability to perform the role defined for them within the intervention. We do, however, have the STOP-Bang from screening, as well as Insomnia Severity Index, sleep diary, and actigraphy at each assessment time point. Thus, we can assess the risk of obstructive sleep apnoea and track symptoms of insomnia in the partners. If we have a couple where both partners report insomnia upon initial contact with the research team, we ask the couple to decide who will enrol as the “client” and who will enrol as the “partner.” While the partner is not required to adopt treatment recommendations themselves, they are welcome to change their behaviour in accordance with treatment if they so desire. This is true whether or not the partner reports sleep problems. Not having formal diagnostic information on the partners limits our ability to assess effectiveness of the interventions in couples where both individuals experience a diagnosed sleep disorder.

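### Allocation is balanced within clinician and client sex but the stated analyses use neither factor, and the sleep-efficiency analyses use no baseline value; precision is lost and the adherence slopes are open to confounding

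*Protocol article*

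**What the plan says.** Under Allocation to treatment conditions, the protocol article names two balancing factors. The first is clinician: "Randomisation occurs within clinicians such that each clinician sees an equal number of clients in each treatment condition". The second is client sex: "Randomisation occurs separately for male and female clients to help ensure equal male:female ratios for each treatment condition".

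Under Statistical tests of hypotheses, it states four analyses:

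- **1A (adherence):** "We will test this with 3 × 5 (group × session) MANOVA".
- **1B (completion):** "Hypothesis 1B will use the Chi-squared test to test the proportion of participants who complete each treatment, with similar follow-ups".
- **2A (adherence and sleep efficiency):** multiple regression "with explanatory variables of group (dummy coded), adherence (in the last week of treatment), and group × adherence interaction". The outcome is the last-week diary level, and the interaction is named as the effect of interest. Follow-ups examine the adherence effect within each group.
- **2B (sleep efficiency, PA-CBTI versus i-CBTI, at post-treatment and 6 months):** Sobel mediation through end-of-treatment adherence. No covariate is named.

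Two other places bear on this. For the Client adherence form, part of the primary outcome set, "therapists rate client adherence on six specific CBTI activities". And the Limitations section says that the baseline "sleep diary and actigraphy data are collected between weeks 1–2 of treatment", conceding that it may not be a true baseline.

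**The concern.** When arms are balanced within a prognostic factor, that factor no longer contributes to the sampling variability of the difference between arms. If the model then leaves the factor out, its variance stays in the residual. The model's standard error is larger than the true variability, the test rejects less often than its nominal level, and power that the design has already paid for is not used. A clinician effect is most plausible for the CAF, because the clinician is also the rater and differences in leniency enter the score directly.

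The baseline issue is of another kind. In the randomised comparison of sleep efficiency, omitting baseline leaves a valid but less precise estimate. Adherence, however, is not randomised. Clients with milder insomnia at entry may both adhere differently and finish with higher sleep efficiency. An adherence slope estimated without any measure of initial severity then mixes the two. This touches the within-group follow-ups of 2A and the adherence-to-outcome path of 2B, on which the claim that adherence drives outcome depends.

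**Working it through.** **Inputs from the article** (Power considerations): N = 120 (40 per group), 3 groups, 5 sessions, f = 0.25, alpha 0.05, power 0.81.

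**Assumptions, because the article gives no figures:** the variance share of clinician and sex, the clinician intraclass correlation (ICC), the number of clinicians, the correlation between sessions, and the share of variance (R²) explained by baseline.

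**1. The stated power.** For the group effect averaged over m = 5 sessions, lambda = f²·N·m / (1 + (m − 1)·rho), with 2 and 117 degrees of freedom. At rho = 0.68, lambda = 0.0625 × 120 × 5 / 3.72 = 10.08 and power is 0.808. At rho = 0.65 power is 0.82, and at rho = 0.72 it is 0.79. So 0.81 is attainable but not fixed by the stated inputs. It is taken as given here; it corresponds to lambda = 10.13.

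**2. Adding clinician and sex.** If they explain a share s of the variance, the unadjusted standard error is too large by 1/√(1 − s), and adjustment raises lambda to 10.13/(1 − s).

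| Share s | SE ratio | Lambda | Power |
|---|---|---|---|
| 0 | 1.000 | 10.13 | 0.81 |
| 5% | 1.026 | 10.66 | 0.83 |
| 10% | 1.054 | 11.25 | 0.85 |
| 20% | 1.118 | 12.66 | 0.89 |

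Giving up 8 error degrees of freedom (117 to 109) lowers power by less than 0.001 at each share above zero.

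**3. Check by simulation.** Blocks of three within clinician × sex, N = 120, 5 or 8 clinicians, 2,500 runs per scenario. The contrast is PA-CBTI versus i-CBTI on a single outcome with a true difference of 0.5 SD.

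| ICC / sex R² | SE unadjusted | SE adjusted | Type I error, unadjusted | Power, unadjusted to adjusted |
|---|---|---|---|---|
| 0 / 0 | 0.223 | 0.223 | – | – |
| 0.10 / 0.02 | 0.221 | 0.210 | about 0.035 | 0.62 to 0.66 |
| 0.20 / 0.02 | 0.220 | 0.197 | 0.027–0.029 | 0.63 to 0.70 |

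The adjusted standard errors match the true sampling SD (about 0.208 and 0.195 in the last two rows); the unadjusted ones exceed it.

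**4. Omitting baseline, group comparison.** With an assumed baseline correlation of 0.5, the residual variance falls to 1 − 0.5² = 0.75. The unadjusted standard error is then 1/√0.75 = 1.155 times the adjusted one, and adjustment is worth 1/0.75 = 1.33 times the sample size. This is a loss of precision only.

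**5. Omitting baseline, adherence slope (2A).** With a true slope of zero and a correlation r between adherence and baseline, the standardised slope is biased by about r × √R². For r = 0.3 this gives 0.3 × √0.25 = 0.15 and 0.3 × √0.40 = 0.19. Simulation agrees: bias 0.15 to 0.19 and false-positive rate 0.15 to 0.23, returning to about 0.05 with adjustment. The group × adherence interaction was not biased when r was the same in the arms (rejection rate 0.04 to 0.06). Its standard error was 0.227–0.232 without baseline and 0.180–0.201 with it.

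**The case against.** Four objections deserve an answer.

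**The article may leave covariates to a fuller document.** Only 2A lists its explanatory variables, and the article calls the trial mixed-effects, which could imply a clinician term. This has some force for 2B, where no model terms are given. It has less for the others: 1A names its factors, 1B names a plain chi-squared test and 2A gives a term list. No mixed model appears among the stated tests. An analysis that followed the text literally would omit these factors.

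**A reader might infer that every planned standard error is wrong.** The documents do not support that. An overstated standard error follows only for the randomised group contrasts, and only if clinician or sex is prognostic. Balance between arms does not by itself imply it for the 2A slope, the 2A interaction or the mediator-to-outcome path. Omitting baseline makes no standard error invalid. A reader might also infer that the 2A interaction is biased; that was not shown under a common correlation across arms.

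**The sizes are assumed.** This stands. The article gives no ICC, sex effect, baseline correlation or number of clinicians. The rater argument applies to the CAF alone, since the diary measures are reported by the client.

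**The week 1–2 diary is a poor main covariate.** This also stands. It is collected after randomisation and after session 1, which the partner attends in two arms, so adjusting for it conditions on something treatment could already have touched.

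**Conclusion.** The point holds in a limited form. The design balances on clinician and sex, and the stated analyses use neither. For 1A, 1B and the group paths of 2B, the consequence is conservative tests and lost power: at the planned effect, 0.81 where 0.83 to 0.89 was available if the factors explain 5% to 20% of the variance, and no loss if they explain none. The omission does not create false-positive group effects. The missing baseline term costs precision in the sleep-efficiency comparisons and leaves the adherence slopes in the 2A follow-ups and the 2B mediator path open to confounding. The size of that confounding depends on how strongly adherence tracks initial severity, which the article does not say. Confidence is high in the omission and its direction, and low in any particular magnitude. The change is worth making because it uses data already collected and the stated power leaves little margin.

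**What to change.** Prespecify the following before analysis:

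- **1A, 2A and 2B:** include clinician and client sex in every model. Clinician can be a fixed effect or a random intercept; a random intercept requires a mixed model in place of the MANOVA.
- **1B:** test completion with an analysis stratified by, or adjusted for, clinician and sex. Fully crossed clinician × sex strata may be sparse for a Cochran-Mantel-Haenszel test, so state in advance how small strata will be collapsed.
- **Sleep-efficiency models (2A, 2B):** adjust for the pre-randomisation ISI as the main covariate. Repeat with the week 1–2 diary sleep efficiency as a sensitivity analysis, stating that it is collected after randomisation and session 1.

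No new data are needed. The cost is a few degrees of freedom, the exact number depending on how many clinicians take part, and a slightly more complex model. The gain from the ISI cannot be stated from the article, which gives no correlation between ISI and diary sleep efficiency.

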#### Blinding

Blinding of participants and clinicians is not possible due to the different structure of the treatment interventions. However, clients are blind to the study hypotheses and outcome variables. Staff who score polysomnography and actigraphy are blind to the treatment condition and hypotheses. There are no other “observer-rated” assessments at post-treatment or 6-month follow-up.

#### Attrition analysis

Analysis of non-completers will be assessed based on those who were scheduled for an initial treatment session. We document the reasons for attrition throughout, and will assess the difference between completers and non-completers, as well as the differential attrition rates between treatment conditions. This forms part of the secondary hypothesis given completion is one of the main outcome variables.

